### *3.1.3. Interventions: food products and quantities, medical treatment and incentives*

#### **Food products and quantities**

Children will receive 500 kcal/day. Food will be distributed fortnightly during a 3 month period. At each visit, a ration will be given on the spot. Mothers will be asked to bring back the empty LNS packs at the next visit to give to the personnel charge of the supplement (not to staff involved in measurements, to ensure blinding).

CSB will be provided in bi-weekly rations, to be prepared at home.

During the entire follow-up, any child developing severe acute malnutrition (WHZ less than – 3 z-scores, MUAC <115 mm or edema) would be referred for treatment of SAM. The following children will be referred to Yako pediatric unit, which is supported by ALIMA, for medical evaluation;

- Children admitted based on WHZ  $\geq$  -3 - and < -2 z-scores who have not reached a WHZ  $\geq$  -2 z-scores at the end of the 3 months intervention
- Children admitted on MUAC  $\geq$  115mm and < 125 mm who have not reached 15% weight gain,
- Children presenting a weight loss  $\geq$  5% from his/her weight at baseline for two consecutive visits.

Should these children receive other nutritional intervention during their hospitalization, they will be withdrawn from the study as failures to respond to treatment. Data obtained after receiving other nutritional intervention than previewed will not be included for data analysis.

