### Outcomes

**Primary outcome:** absolute lean mass increment from baseline to 3 months (deuterium dilution method). **Secondary outcomes:** increase of WHZ to >-2, linear growth, increase in MUAC > 125 mm, physical activity, motor and language milestones development, morbidity, level of hemoglobin, serum acute phase proteins, insulin-like growth factor-1, serum ferritin, thymus size and essential fatty acids, acceptability of and adherence to the products.

 That is, children who did not reach a WHZ  $\geq -2$  or a 15% weight increase if admitted with a MUAC  $\geq 115$ mm et < 125 mm

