## 1.2. Investigational food supplements

Twelve investigational food supplements will be developed based on current available evidence (*[name] KF et al, 2009; Golden M, 2008*) and international guidance (WFP, WHO, MSF, ALIMA). These include improved CSB based supplements (iCSBS) and LNS combining different soy qualities and different amounts of total protein provided by dry skimmed milk (DSM), as follows:

- 3 iCSBS based on dehulled soy, with either 0%, 20% or 50% of total proteins provided by DSM
- 3 iCSBS based on soy isolate, with either 0%, 20% or 50% of total proteins provided by DSM
- 3 LNS based on dehulled soy, with either 0%, 20% or 50% of total proteins provided by DSM
- 3 LNS based on soy isolate, with either 0%, 20% or 50% of total proteins provided by DSM

Thus a total of 12 products, 6 in the form of LNS and 6 in the form of CSB.

---

 0%, 20% and 50% of total protein provided by DSM corresponds to 0%, 8% and 20% of total weight.

Both types of product will comply with the WHO technical note “Supplementary foods for the management of moderate acute malnutrition in infants and children 6 – 59 months of age”(WHO 2012)

The products will not have the same nutrient density per 100g, but will provide the same total amount of protein and micronutrients per daily serve (130g of CSB or 92g of LNS).

The fatty acid profile will be similar in all twelve products and the same supplier for the main raw material, dehulled soya and soy isolate, will be used for both LNS and CSBs.

A vitamin and mineral premix will be designed for all products and will meet the quantities specified in the WHO technical note. Some adjustments will be necessary between products because e.g. dry skim milk in larger quantities will be a significant contributor of e.g. calcium, potassium and phosphorous, and because the concentration of certain vitamins decreases during the preparation of CSB. The aim is a uniform micronutrient composition across all products for final consumption.

For a detailed description of the composition of the products, please see annex 2.

LNS will be provided in individual packaging, ready for consumption with no need for preparation or cooking. All LNS individual packs will have similar packaging, whatever the type of soy or the milk content, and will only differ by a number.

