iCSBs fortnightly food rations will be delivered to the caretakers in bags of 1.7 kg which corresponds to a bi-weekly ration (130 g/child/day). All iCSB bags will have similar packaging, whatever the type of soy or the milk content, and will only differ by a number. iCSBs have to be consumed as a porridge or gruel. The flour should be mixed with an appropriate proportion of clean water followed by a cooking time at simmering point from five to maximum ten minutes.

For children with MAM, it is usually recommended to provide a food supplement daily ration of 75 kcal/kg that covers the daily micronutrients requirements (*Manary et al, 2008*). In addition to the usual diet, this quantity is sufficient to promote catch up growth. However, in order for possible intra-household food sharing to be taken into account, many organizations usually distribute a food supplement providing at least 1000 kcal/day, which appears relatively high for children with MAM (*[name] S et al, 2009*). Children with MAM (weight-for-height  $\geq -3$  and  $< -2$  Z-scores ) and measuring between 65 and 87 cm are expected to weigh between 5.5 and 10.4 kg (WHO growth standard). These children would therefore need a food supplement daily ration of 413 kcal (5.5 kg \* 75 kcal/kg) to 780 kcal (10.4 kg \* 75

kcal/kg). In this study, children will receive a fixed daily ration equivalent to 500 kcal/day. The same amount of energy will be provided for all food supplements.

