## **Questionnaire**

At baseline, socio- demographic and medical characteristics of the participants will be collected using an interviewer-administered baseline questionnaire. At each subsequent fortnightly/monthly visit, caretakers will answer a questionnaire about morbidity. Some questions will also assess the adherence to the food supplement (quantities consumed). In addition, all data on morbidity as collected during the clinical examination by a nurse (symptoms, diagnosis and treatments prescribed) will be recorded in a case-report form. All serious AE will be immediately reported to the study supervisor. Childcare behaviors related to supplementary feeding and adherence to and acceptability of the products will furthermore be explored (as described in the section 3.3). The provisional list of information that will be collected is presented in annex 7. In addition dietary data will also be collected at inclusion, 3 and 6 months.

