### 3.2. Child care practices related to supplementary feeding and the perception, acceptability of and adherence to the food

Childcare practices related to supplementary feeding and perceptions, acceptability of and adherence to the foods will be explored by doing structured observational studies, in-depth and semi-structured interviews, questionnaires as well as Focus Group Discussions (FGD).

**Structured Observations** are included in order to gain a realistic picture of actual practices rather than just the informants' views on "correct" perceptions. In this way, this part of the study aims at exploring social activities and the meaning given to these by observing phenomena in their natural setting on a limited subsample.

A trained local assistant will be observing the caretakers and children in the private home of the family during daytime to explore child care practices related to feeding and adherence to treatment and will include observations on particularly:

- *Caregiver's feeding behaviors* such as frequency of and time devoted for supplementary feeding of the child, interaction with the child during feeding incl. level of supervision and encouragement and hygiene behaviors related to the feeding situation (Dearden et al. 2009; Flax et al. 2010)
- *Child feeding practices*, such as the position of the child during the feeding situation, the way the child is fed and utensils used for feeding and how and when the supplementary diets are consumed (i.e. as snacks or as a meal, as individual diets or shared with other household members (Pelto et al. 2003; Flax et al. 2010; Shankar et al. 1998)i
- *Adherence to the treatment* in terms of compliance to treatment and to which degree the products are stored, prepared and distributed according to recommendations.

It is planned for the local assistant to spend three consecutive days (during daytime) in the household of each of the participants. For practical reasons, 20 participants will be randomly selected from one of the recruitment sites (10 participants from the LNS groups, 10 participants from the CSB groups)

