**Questionnaires:** At the first follow-up visit (2 weeks into supplementation) all caretakers of participants in the study will be asked questions on the acceptability of and adherence to the products, following a structured questionnaire. This questionnaire will include questions on the perception of the quantity, appearance, taste, smell and consistency of the products and will be assessed according to a five-point Hedonic scale (from “5” – “like very much” to “1” – “dislike very much”). Furthermore questions regarding the health of the child and breastfeeding patterns during supplementation as well as feeding practices will be asked.

With the assumption that acceptability of new foods increases, if it is served for a longer period of time, the questionnaire will be repeated at the end of the supplementation period (at 3 months). Furthermore caretakers will at this point be asked questions related to food security based on the assumption that foods may be more acceptable in households with high food insecurity. Food security will be assessed using questions from the Household

Food Security Access Scale (HFIAS), and the level of food insecurity for each household will be classified into four levels of food insecurity (food secure, mildly food insecure, moderately food insecure, severely food insecure) (Annex 8). Furthermore a trained research assistant will administer the questionnaire in the local language.

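### Only LNS caretakers are asked to return empty packaging, a trial-made difference between the two foods that could be removed cheaply

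*Combined protocol and SAP*

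**What the plan says.** Section 3.1.3 (Food products and quantities) sets out the fortnightly distribution. For LNS: "Mothers will be asked to bring back the empty LNS packs at the next visit to give to the personnel charge of the supplement". The stated reason for handing them to those staff, and not to the measurement team, is blinding. For the flour the same section says only: "CSB will be provided in bi-weekly rations, to be prepared at home".

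Section 1.2 gives the packaging. "LNS will be provided in individual packaging, ready for consumption with no need for preparation or cooking", whereas "iCSBs fortnightly food rations will be delivered to the caretakers in bags of 1.7 kg", at 130 g per child per day.

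Adherence is listed among the secondary outcomes in the Summary ("acceptability of and adherence to the products"). The methods given for measuring it cover both foods:

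- At each visit, in section 3.1.11: "Some questions will also assess the adherence to the food supplement (quantities consumed".
- At two weeks, repeated at three months, in section 3.2: "all caretakers of participants in the study will be asked questions on the acceptability of and adherence to the products".
- Home observation over three days in a small sample, also in section 3.2: "10 participants from the LNS groups, 10 participants from the CSB groups".

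Section 3.1.9 states that participants are not blinded to food type and refers to annex 6 for the management of the products. Section 3.1.13 puts both foods in one primary model, with pairwise comparisons within and across the two arms.

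**The concern.** A caretaker who expects to hand back empties every two weeks has a regular reminder to use the product and some reason to report having used it. In the supplied text that reminder exists for LNS and not for iCSB. Cooking, taste and packaging belong to the foods, and an effectiveness trial rightly includes their consequences. A return request is added by the trial, and randomization does not remove a procedural difference that begins after allocation.

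Two results could be touched. The first is the LNS-iCSB contrast in lean mass, if the request raises actual intake of LNS. The second is any LNS-iCSB comparison of adherence, if it changes how LNS caretakers answer the shared questions. Section 3.1.14 names poor adherence as a possible limitation but does not mention this difference between the foods.

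**Working it through.** **1. The provisions side by side**

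| | LNS | iCSB |
|---|---|---|
| Distribution (3.1.3) | Fortnightly | Fortnightly |
| Unit issued (1.2) | Individual packs | 1.7 kg bag |
| Return of packaging (3.1.3) | Requested | Not mentioned |
| Returned items counted or recorded | Not stated | Not applicable |
| Adherence questions (3.1.11, 3.2) | All caretakers | All caretakers |
| Home observation (3.2) | 10 households | 10 households |
| Education stressing the prescription (3.1.14) | Yes | Yes |

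The return request is the only row in which trial procedure differs.

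**2. The plan's own sample size**

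Section 3.1.7 uses n = 16 s²/d² with d = 0.4 SD: 16/0.16 = 100 per cell. Allowing for 25% loss, 100/0.75 = 133.3, rounded up to 134; 12 × 134 = 1608. These figures reproduce and are not affected by this point. Six cells per food type give 6 × 100 = 600 completers on each side of the LNS-iCSB contrast.

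**3. How sensitive the lean-mass contrast is**

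SE = √(2/600) = 0.0577 SD. The detectable difference at 80% power and two-sided 5% is (1.96 + 0.84) × 0.0577 = 0.16 SD.

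The documents give no size for a reminder effect, so the shift b below is assumed. The chance of a significant difference when the foods are truly equal is Φ(b/SE − 1.96) + Φ(−b/SE − 1.96):

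| Assumed shift b (SD) | Chance of a false difference |
|---|---|
| 0 | 5% |
| 0.02 | 6% |
| 0.05 | 14% |
| 0.10 | 41% |
| 0.15 | 74% |

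To link b to adherence, assume that a full supplement is worth 0.4 to 0.8 SD and that the request opens a 10-point adherence gap. Then b = 0.10 × 0.4 = 0.04 to 0.10 × 0.8 = 0.08 SD, which gives about 11% to 28%. The calculation ignores covariates, centre effects and multiplicity adjustment.

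**4. How sensitive reported adherence is**

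With an assumed SD of 25 percentage points, the SE of a difference in mean adherence is 25 × √(2/600) = 1.4 points. An assumed 5-point shift in LNS answers would be about 3.5 SE. For SDs of 15 and 35 the SE is 0.9 and 2.0 points.

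**5. A trap if returns are quantified**

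A natural measure is daily rations used divided by days since the last visit. Section 1.2 gives a 1.7 kg bag at 130 g a day: 1700/130 = 13.1 rations. Fourteen days would take 14 × 130 = 1820 g. A fully adherent iCSB child would therefore score at most 13.1/14 = 93%. If LNS children are issued 14 packs, a number the plan does not state, that measure alone creates a gap of about 6.6 points between foods. Amount used over amount issued does not have this fault.

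**The case against.** The strongest reply is that the plan measures adherence in the same way for both foods, and this stands. A reader might infer from the pack return that LNS adherence is checked by a count while iCSB adherence rests on verbal report. The documents do not support that: no section says that packs are counted, recorded or reconciled, and the questionnaires and home observations cover both foods.

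A reader might also infer that a per-protocol analysis would exclude different kinds of children by food type. Section 3.1.13 says only that such an analysis might be done after excluding protocol violations, and it sets no adherence rule.

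Further points also stand. The primary outcome is a deuterium measurement by an assessor blinded to food type, so biased reporting cannot reach it and only a change in actual intake could. Both foods share the visit schedule, the observed first dose and the adherence messages, so any extra effect of carrying back empties may be small. Annex 6 may well specify returns for iCSB, so the absence can be asserted only for the supplied text.

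What the reply does not remove is the asymmetry itself. The effectiveness aim in section 3.1.14 covers practical differences between foods, but it does not clearly cover a request that the trial makes for one food only. If packs are not counted, the plan keeps the prompt without stating its purpose.

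**Conclusion.** The point holds in a limited form. In the supplied text, a fortnightly return request is written for LNS only, within an open comparison that forms part of the primary analysis. It may prompt use, or influence answers to the shared adherence questions, in one food type. Its size is unknown and a direction towards LNS is presumed, not shown.

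The figures above show only that a contrast with about 600 children per side is sensitive to small procedural shifts: 0.05 SD would move a 5% error rate to about 14%. They rest on assumed shifts and an assumed SD, and they are not evidence that a bias exists. It would be wrong to conclude that the LNS-iCSB result is biased. Soy and milk comparisons within each food type are unaffected, because all six products of a type share the same procedure. This is a cheap improvement, not a defect that threatens the trial.

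**What to change.** - In section 3.1.3, make the same request for both foods: LNS packs, and iCSB bags with any leftover flour, are brought back at each fortnightly visit and handed to supplement staff in the same opaque carrier. The common carrier also helps to keep measurement staff unaware of food type.
- State whether returned items are counted or weighed and what the result is used for, and bring annex 6 into line.
- If returns are quantified, define use as amount used divided by amount issued in both foods, not per day since the last visit.
- Reconcile the bag weight, daily amount and ration period in section 1.2.
- Base any LNS-iCSB adherence comparison on the common questionnaire unless returns are quantified in the same way for both foods.
- If the request stays with LNS alone, list the difference in section 3.1.14 as a limitation of the LNS-iCSB contrast.

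The cost is a change of wording, a little more effort for iCSB caretakers and, if leftovers are quantified, a short weighing step by supplement staff already in place. Returns do not detect sharing within the household for either food.

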| Serious Adverse Events                                                                                  | Local Foods                                          | Until the end of treatment                                                                        | - Outcome of the treatment
- Anthropometric measurements and clinical assessment until end of treatment                                   |
| Other                                                                                     |                                                      |                                                                                                   |                                                                                                                                              |
| Transfer to the ATFC or ITFC,                                                                           | RUTF or food as provided at the ITFC or the hospital | Until the end of treatment                                                                        | - Outcome of the treatment
- Anthropometric measurements and clinical assessment until end of treatment                                   |
| Hospitalization                                                                                         | Continue intervention                                | Until the end of treatment                                                                        | - Medical follow-up
Outcome of the treatment
- Anthropometric measurements and clinical assessment until end of treatment  |

 Participants who withdraw informed consent or were lost to follow-up will not receive further incentives. Other participants will receive the incentives according to the planned timing at the start of the study.

 Children receiving other nutritional intervention (which is not part of Study) after being referred, they will be considered as failure to respond to treatment, and data obtained after receiving other nutritional intervention than previewed will not be included for data analysis

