### *3.1.7. Sample size*

In the absence of information on the increase of LBM from 0-3 months among children with MAM in this age group, we assume that a 0.4 SD difference in change/increase in lean body mass between groups as clinically relevant. The sample size per group,  $n$ , required to detect a change,  $d$ , in a continuous variable with standard deviation,  $s$ , with alpha set at 5% and a 80% power, is  $16*s^2/d^2$ . Hence, to detect a 0.4 SD greater increase in lean body mass between 2 products/cells, we will need 100 children in each group. To allow for a 25% expected loss to follow-up/drop-out in the nutritional program in Burkina Faso, we will include 134 children in each of the 12 intervention groups (cells) then  $12 \times 134 = 1608$  children.

Considering a recruitment rate of 54 children with MAM per month per CSPA, the recruitment is therefore expected to last about 6 months and will be limited five CSPA (i.e., 54 children with MAM \* 6 months \* 5 CSPA = 1620 children).

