### 3.1.13. *Data analysis*

The main effectiveness criterion will be the mean change in lean body mass after 3 months of supplementation (absolute increase expressed in kg). The primary analysis will be conducted in the intention to treat (ITT) population and will therefore include all randomized subjects having at least one exploitable baseline and 3 months LBM measures,. The primary analysis will be conducted by means of a single statistical analysis including both main arms, ie LNS and iCSB:

- A three-way analysis of variance (ANOVA) will be used to evaluate if the two interventions modify the effect of dehulled soy and soy isolate at different levels of milk content.
- The ANOVA will also include LBM at baseline as well as a number of additional explanatory (age, sex, MUAC, WHZ, season) that adjust for potential differences present in the study population. To adjust for variation between centers random effects for each centre are also included in the model. Thus, the statistical model will be based on a linear mixed model.
- Pairwise comparisons of means within and across the two arms will be done using the linear mixed model. Multiplicity will be taken into account by adjusting all pairwise comparisons.
- The effect of supplementation, ie. the difference in mean changes in LBM at 3 months of each group will be presented in terms of estimated means with 95% confidence intervals.

All other statistical analyses of the primary endpoint, ie other study populations, sub-group analysis, and inside-the-table comparisons, and all statistical analyses of secondary endpoints, will be considered secondary analyses. These include:

- Evaluation of the effect of the type of soy by comparing, in the LNS and the iCSBs groups separately, the mean increase in LBM at 3 months over the two groups of soy quality (dehulled soy i.e. 3 groups merged, soy isolate i.e. 3 groups merged).
- Evaluation of the effect of the milk protein content by comparing, in the LNS and the iCSBs groups separately, the mean increase in LBM at 3 months over the three groups of milk protein content (i.e. 2 groups merged for each level of milk).
- Analysis might also be conducted among the subgroup of participants presenting these 2 LBM measurements and the per-protocol population (i.e. excluding participants with violation of protocol).

For all secondary analyses, no adjustment for multiplicity is planned.

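### Children who respond poorly and are given other food before month 3 drop out of the primary comparison, although it is labelled intention-to-treat

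*Combined protocol and SAP*

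**What the plan says.** Section 3.1.3 (Food products and quantities) sends any child who develops SAM at any point in follow-up for SAM treatment. It refers three further groups for medical evaluation: children admitted on WHZ who have not recovered at the end of the three months, children admitted on MUAC who have not gained enough weight, and children whose weight is 5% or more below baseline at two visits running. Those given other nutrition are withdrawn as failures, and "Data obtained after receiving other nutritional intervention than previewed will not be included for data analysis".

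The second footnote to Table 1 (section 3.1.6) repeats the rule for referred children: "they will be considered as failure to respond to treatment", with the later data again left out. The Table 1 row for transfer to a therapeutic feeding centre provides RUTF or the centre's food. The only measurements it lists are "Anthropometric measurements and clinical assessment until end of treatment"; the deuterium test is not among them.

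Section 3.1.13 states: "The primary analysis will be conducted in the intention to treat (ITT) population". It then defines that population as randomised children with usable LBM at both baseline and month 3. The only other populations are optional: children with both LBM measurements, which is the same set, and per-protocol. No imputation or missing-data sensitivity analysis is named. Section 3.1.6 does not replace withdrawals. The closing summary of changes to the statistical analysis plan leaves the rule as it is.

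**The concern.** SAM and sustained weight loss occur after randomisation and may be consequences of the allocated product. Removing a child's month-3 value because of them makes inclusion in the primary analysis depend on response. Randomisation then no longer protects the comparison, and the intention-to-treat label does not describe what is analysed.

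It also conflicts with section 3.1.14, which says the trial studies effectiveness, practical effects included, rather than efficacy. The same section concedes that withdrawal may differ between groups, which is the condition under which the exclusion biases the result. The loss cannot be repaired at analysis if the month-3 test was never done.

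**Working it through.** **1. The plan's own figure.** Section 3.1.7 uses "alpha set at 5% and a 80% power" and a target of 0.4 SD.

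- Plan's rule: 16 × 1² / 0.4² = 100 per cell, as stated ("we will need 100 children in each group").
- Usual two-sided formula: 2 × (1.960 + 0.842)² / 0.4² = 98.1, so 99.
- With 25% loss: 100 / 0.75 = 133.3, so 134; and 12 × 134 = 1608.
- Power for 0.4 SD at 100 per cell: Φ(0.4/√(2/100) − 1.960) = 80.7%.

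The sample size reproduces. The 25% allowance restores numbers, but does nothing about which children are lost.

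**2. Who is affected.** In every row, only children who actually receive other food are affected, and data from before the switch stay in.

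| Route | Timing | Primary outcome | Month 4–6 data |
|---|---|---|---|
| SAM, then other food | any time | lost if before month 3 | lost after the switch |
| Weight 5% or more below baseline at two visits running, then other food | any time | lost if before month 3 | lost after the switch |
| Not recovered, then other food | end of month 3 | mostly kept, as the LBM test is due then | lost after the switch |

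For MUAC admissions, section 3.1.3 gives no time for the weight-gain criterion; the Summary places non-recovery after three months. LBM is not measured at month 6, so the month 4–6 losses concern secondary outcomes only.

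**3. Formula.** In one arm, let p be the proportion switched before month 3 and g the gap (mean gain of those kept minus mean gain of those switched). The mean over all randomised children is (1 − p) × kept + p × switched. The mean in the analysed set therefore exceeds it by p × g. Between arms A and B, the bias is p_A × g_A − p_B × g_B, or (p_A − p_B) × g with a common gap. It is zero if switching and gaps are equal.

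**4. Numbers.** The documents give neither p nor g, so the inputs below are assumptions. Share is bias / 0.4. Power is Φ((0.4 − bias)/√(2/100) − 1.960), where the truly worse arm has more switches.

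| Difference in switching | Gap (SD) | Bias (SD) | Share of 0.4 SD | Power, 100 per cell |
|---|---|---|---|---|
| 1 point | 0.5 | 0.005 | 1% | 79.8% |
| 2 points | 1.0 | 0.02 | 5% | 76.6% |
| 5 points | 0.5 | 0.025 | 6% | 75.5% |
| 5 points | 1.0 | 0.05 | 12.5% | 69.7% |
| 10 points | 1.0 | 0.10 | 25% | 56.4% |
| 10 points | 1.5 | 0.15 | 38% | 42.4% |
| 10 points | −0.5 | −0.05 | −12.5% | 88.9% |

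The last row is the case where therapeutic feeding has lifted switched children above the others.

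**5. Pooled contrast.** For LNS against iCSB, with 6 × 100 = 600 evaluable per side, the SE is √(2/600) = 0.058 SD. A bias of 0.005 SD is 0.09 SE, 0.025 SD is 0.43 SE and 0.10 SD is 1.7 SE. With no true difference, 0.10 SD would make a nominal 5% test reject about Φ(1.732 − 1.960) = 41% of the time. Between two single cells, the same bias gives about 11%.

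**6. Cross-check with a selection model (assumed).** Failure means falling below a common threshold t on a normal scale that correlates ρ with LBM gain. The true difference is 0.4 SD on both scales. The kept mean is μ + ρ × φ(a)/(1 − Φ(a)), with a = t − μ. With 5% failing in the better arm, 10.7% fail in the worse arm.

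- ρ = 0.5: 0.054 − (−0.4 + 0.103) = 0.35 SD, 12% attenuation, power 70%.
- ρ = 1: 0.109 − (−0.4 + 0.206) = 0.30 SD, 24% attenuation, power 57%.

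This model gives switched children no benefit from the other food.

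**The case against.** **Reach.** A reader might infer that the primary contrast becomes a comparison of responders, or that month 6 is close to one. The documents do not support either. Non-recovered children who reach the month-3 visit keep their LBM value. Referral is for medical evaluation, exclusion needs actual receipt of other food, and the hospitalization row of Table 1 continues the intervention. No figure says how many would switch. Nor are data deleted wholesale: only data from after the switch are left out. This objection stands and limits the point to switches before month 3 and to month 4–6 secondary outcomes.

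**Direction.** A reader might also infer that the bias always favours the worse product. That requires unequal switching, and switched children who are still behind at month 3. Once they have had therapeutic food they may not be, and the sign would then reverse. This stands too, but it is also a reason to measure them, because the plan as written cannot show which case applies.

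**Size.** All products supply the same energy, protein and micronutrients per daily serving, so a 10-point difference in switching is not an obvious base case. Covariate adjustment in the model might also absorb part of the bias. Both are fair, and the range accordingly starts at 1 point.

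**Existing safeguards.** SAM, hospitalization and death are listed outcomes, and switched children are labelled failures, so failures can be counted by arm. Nothing, however, connects those counts to the primary comparison.

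**Measurement.** LBM rests on standard hydration values for age and sex, and the deuterium section warns that disease may delay equilibration. Values may be least reliable in children with oedema or illness. This is a real cost of the remedy.

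**Conclusion.** The point holds in limited form. Children switched to other food before month 3 leave the primary comparison because of a poor response after randomisation, contrary to its intention-to-treat label and to the effectiveness aim, and no planned analysis offsets this. Children referred for non-recovery at the end of month 3 mostly keep their primary outcome, but lose later secondary data if they are then given other food.

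Under assumed differences of 1 to 10 points and gaps of 0.5 to 1.5 SD, the bias is about 0.005 to 0.15 SD, from negligible to 38% of the target. These figures assume a common gap, 100 evaluable children per cell and no gain from covariate adjustment. Neither size nor direction can be fixed from the documents. The conclusion that does not depend on these assumptions is that the plan fails to secure the data needed to settle the question.

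**What to change.** - In section 3.1.3 and Table 1, keep the month-3 deuterium test and the month-3 and month-6 assessments, on their original dates, for every randomised child without withdrawal of consent, whatever food is received.
- In section 3.1.13, include these data in the primary analysis as randomised. Keep exclusion after other nutrition as a sensitivity analysis.
- Where month-3 LBM is still missing, add a delta-adjusted analysis over values of both signs.
- Report switches to other nutrition by arm.
- Reconcile section 3.1.3, which calls these children withdrawn, with Table 1, which lists transfers under a separate heading from withdrawals and continues follow-up.

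Referral and feeding rules are unchanged. The cost is a small amendment and visits already scheduled, for the children who switch. There are two downsides. Other food may dilute or distort the product contrasts, which the sensitivity analysis would help to show. Deuterium-based LBM may also be less reliable in children with oedema or illness.
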